### Strategies to improve adherence to interventions {11c}

Adherence to the follow-up visit schedule is promoted by facilitating the study visit within 7–10 days after surgery and telephone interview at 3 months and 12 months post-op.

### Relevant concomitant care permitted or prohibited during the trial {11d}

All patients in both arms will be given standard recommendation to avoid intensive physical activity for 2 weeks post-op. Standard wound care will be explained to patients in both groups.

### Provisions for post-trial care {30}

There are no provisions for post-trial care.

### Outcomes {12}

Participants will complete measurements for primary and secondary endpoints at baseline, 7 days post-baseline (post-intervention), 3 months, and 1 year post-baseline (follow-up) (Table 1).

#### Primary outcome

The primary endpoint is the recurrence rate in 1-year follow-up.

#### Secondary outcomes

Besides primary outcome secondary outcomes will also be noted.

1. Pain sensation assessed with Visual Analog Scale measured during hospital stay, 7 days post-op, 3 months, and 12 months after surgery.

2. Incidence of other complications (seroma, hematoma, infections) assessed during hospital stay, 7 days post-op, 3 months, and 12-months after surgery.

7 day post-op visit will be performed by a surgeon blinded to the arm allocation. During the visit, another form will be filled and placed in encoded envelope. Three months post-op and 1-year post-op follow-up, a phone call will be performed by the Study Secretary blinded to the allocation. Telephone call after inguinal hernia surgery is a verified and validated form of follow-up [5, 6]. If there are any concerns, the patient will be asked to attend an outpatient appointment.

Participant demographics including general medical history, body mass index, co-morbidities, age, sex, smoking status, history of hernia repairs, and family history of hernias will be noted and placed in sealed coded envelopes.

### Participant timeline {13}

All patients undergoing elective inguinal hernia repair, meeting the inclusion criteria for the study, will be asked to participate and given informed written consent. After creating a pneumoperitoneum and placing a vision trocar, the hernia defect will be measured. If the presence of a simple M3 hernia (or a complex M3 hernia with a component of an oblique hernia) is confirmed, full inclusion in the study will take place. After the next stages of the operation, i.e., placement of working trocars, release of adhesions, and dissection of the preperitoneal space with reduction of the hernial sac, the stage of random allocation to the study arms will take place by opening the envelope and learning the technique to be used in a given participant. After the procedure, the surgeon will fill out the researcher’s card and place the operating protocol in a prepared coded envelope. The participant will receive information about full inclusion in the study and full follow-up. A follow-up visit 7–10 days after the surgery will take place in the hospital outpatient clinic, during which further information about the health condition will be collected, and a physical examination will be performed. Both groups will receive the same standard postoperative recommendations. Subsequent follow-ups (3 months and 12 months after) will take place through a telephone conversation made by study secretary blinded to the method used. Detailed timeline is presented in Table 1.

### Sample size {14}

Statistical analysis was performed to adjust the sample sizes. The trial was planned as non-inferiority study with test power = 80%,* p*-value = 0.05, and threshold for clinical significance = 8%. A percentage loss of 10% was assumed. Recurrence rate was assumed to be 4% based on literature data. Based on those assumptions, minimal sample size in both arms was established at 83–102.

### Recruitment {15}

Recruitment commenced in February 2023. Participants are recruited in centers managed by the Sponsor and by Collaborators. Despite inguinal hernias being a common disease and over 60–70 thousand inguinal hernia repairs are being performed in Poland annually, M3 and complex hernias are rather rare. To obtain required number of participants, a multicenter study is needed and that is why 11 large surgery centers in Poland, proficient in laparoendoscopic groin hernia repairs (performing at least 80 TAPP/TEP procedures a year), were selected for this study. Patients will be encouraged to complete follow-up via talk and discussion with surgeon. 10% of lost to follow-up is predicted.

## Assignment of interventions: allocation

### Sequence generation {16a}

Randomization will be performed with the use of the Clinical Trial Randomization Tool (National Cancer Institute) on 1:1 basis by Study Secretary. Based on randomization, 204 envelopes will be prepared, each with a unique code number. Inside, apart from blank research cards to be completed, there will also be a smaller envelope with the type of technique to be used during the procedure. Participants, the Study Secretary, and surgeons will be blinded in terms of allocation to individual arms (until the envelope is opened). Unblinding will take place at the end of the trial via phone call (or ambulatory visit if one will be scheduled) by Study Secretary.

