## Methods: participants, interventions, and outcomes

### Study setting {9}

Eleven large surgery centers in Poland, proficient in laparoendoscopic groin hernia repairs (performing at least 80 TAPP/TEP procedures a year), were selected for this study (Table 1 and Fig. 1). List of study sites (collaborators) is given in the Organizational Structure and Responsibilities section at the end of document. Recurrence rate in 12-month follow-up was set as a primary outcome. Swissmed Hospital in Gdańsk, Poland, is responsible for the coordination of MEFI Trial, as well as, for conducting the phone call follow-up protocol. Also, it is the central point of contact for study participants and surgeons. Study participants will be recruited in collaborating hospitals and in coordinating unit. Study Secretary and Study Chief will be known to participants and they will be given their e-mail and phone number to stay in constant contact. Study Chief and Study Director along with Study Secretary and two volunteers from collaborators centers will be form the Trial Steering Committee. The Trial Steering Committee will meet once a month to exchange information and evaluate recent data. Study group will also have access to WhatsApp group and Facebook closed group to exchange comments/observations and provide organizational support. Study Chief, Study Director, and Study Secretary will be available to all study participants and other collaborators 24/7. Data will be managed by each surgeon designated from collaborators centers. All designated surgeons will form the Data Management Team.

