### Implementation {16c}

Enrolment will be performed by Study Secretary. Each prepared envelope will have specific number previously generated by a computer program and will be associated with the technique performed (fixation/non-fixation). The name of the technique and, therefore, assignment to intervention will be placed in the proper envelope. Surgeon will not be aware of the technique he should perform before opening the envelope.

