## Assignment of interventions: blinding

### Who will be blinded {17a}

Trial participants and Study Secretary performing phone call follow-up visit will be blinded to the method used. Surgeon will be blinded for as long as possible (after the dissection, reduction of hernia sack, and creation of preperitoneal space are achieved).

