### Methods in analysis to handle protocol non-adherence and any statistical methods to handle missing data {20c}

Most important stages of the surgical procedures will be recorded to make sure proper technique was applied. Video files will be sent to a dedicated protected server and files will be named after participant code number. Trial Steering Committee will have access to those files and will evaluate them once a month to make sure no crucial errors in technique are made.

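### The Study Secretary who ascertains recurrence by phone is called blinded, but is also assigned to run the randomization and sits on the committee that reviews code-labelled operation videos

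*Protocol article*

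**What the plan says.** **Blinding.** Who will be blinded {17a} states: "Trial participants and Study Secretary performing phone call follow-up visit will be blinded to the method used". The abstract (Methods), Secondary outcomes under {12} and Participant timeline {13} say the same of the person making the 3- and 12-month calls. The primary endpoint is recurrence over one year. After the clinic visit at 7–10 days those calls are the only routine contacts, and an outpatient appointment follows only if there are concerns.

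**Randomization.** Sequence generation {16a} states: "Randomization will be performed with the use of the Clinical Trial Randomization Tool (National Cancer Institute) on 1:1 basis by Study Secretary". From this, 204 coded envelopes are prepared. Implementation {16c} says that each envelope's number "will be associated with the technique performed (fixation/non-fixation"). Section {16a} also says: "Participants, the Study Secretary, and surgeons will be blinded in terms of allocation to individual arms (until the envelope is opened").

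**Committee and videos.** Study setting {9} says that the Study Chief and Study Director, "along with Study Secretary and two volunteers from collaborators centers will be form the Trial Steering Committee"; {5d} repeats this membership. Section {20c} says of the operation videos that "files will be named after participant code number" and that the "Trial Steering Committee will have access to those files and will evaluate them once a month". Intervention description {11a} makes dissection and mesh placement the part to be recorded.

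**Unblinding.** Sections {16a} and {17b} place it at the end of the trial (12 months), by phone call or clinic visit, and {16a} has the Study Secretary do it.

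**The concern.** One role is assigned both the tasks that expose allocation and the assessment that must be free of it. The person who runs the randomization has at some point had the link between code and technique. A member of a committee that watches mesh placement under the participant's code can see the arm directly, because a flat mesh glued at set landmarks looks different from a shaped mesh without glue.

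What is at stake is the ascertainment of the primary endpoint. Recurrence after the first clinic visit comes to light through a phone conversation and, if there are concerns, a visit. If knowledge of the arm affected how symptoms were probed or which patients were called in, recurrences could be found at different rates in the two arms. In a non-inferiority trial, under-detection in the experimental arm favours the conclusion that the authors say they expect (abstract, Discussion).

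**Working it through.** **1. Roles side by side**

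| Task | Who | Where | Exposes the arm? |
|---|---|---|---|
| Runs the randomization | Study Secretary | {16a}, {16c} | Yes, unless a safeguard exists; none is described |
| Monthly review of code-named mesh-placement videos | Steering Committee, including the Study Secretary | {9}, {5d}, {11a}, {20c} | Yes, unless recused; no recusal is described |
| Access to interim results | Steering Committee | {19}, {21b} | Only if split by arm; not stated |
| Enrolment | Study Secretary | {16c} | No; the surgeon learns the arm in theatre |
| Calls at 3 and 12 months | Study Secretary, stated blinded | {12}, {13}, {17a} | Must not know the arm |
| Unblinding at 12 months | Study Secretary | {16a}, {17b} | Order relative to the outcome is not stated |

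Either of the first two rows is enough to conflict with {17a}. The video route recurs through follow-up and does not depend on who keeps the list.

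**2. The plan's own sample size.** Inputs from {14}: recurrence 4%, margin 8% (taken as absolute), power 80%, level 0.05, loss 10%.

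n = 2p(1 − p)(z_α + z_β)² / Δ²

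- One-sided 0.05: 2 × 0.04 × 0.96 × (1.645 + 0.842)² / 0.08² = 74.2, so 75 per arm. Adding 10% gives 82.5, so 83; dividing by 0.9 gives 84. The stated lower figure of 83 reproduces.
- One-sided 0.025: 94.2, so 95 per arm, and 105 or 106 after loss. This is near the stated 102 but not equal to it.

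The sidedness of the 0.05 is not stated, so both levels are carried below. Nothing here depends on which sample size is right.

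**3. How few events matter.** The total of 204 gives 102 per arm, or 102 × 0.9 = 91.8, about 92, after 10% loss. At 4% the expected recurrences are 0.04 × 92 = 3.7 or 0.04 × 102 = 4.1, so about 4 per arm.

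Newcombe upper limit for non-fixation (E) minus fixation (C), where u and l are the Wilson limits:

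U = (p_E − p_C) + √[(u_E − p_E)² + (p_C − l_C)²]

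Example, n = 92, two-sided 95%, 4 (C) v 5 (E): p_C = 0.0435, l_C = 0.0170, p_E = 0.0543, u_E = 0.1210. U = 0.0109 + √(0.0666² + 0.0264²) = 0.083, above 0.08.

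Upper limits in percentage points, with 4 recurrences in the control arm:

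| n per arm | Level | 4 v 4 | 4 v 5 | 4 v 6 | 4 v 7 | Extra events to exceed 8 |
|---|---|---|---|---|---|---|
| 92 | two-sided 95% | 6.8 | 8.3 | 9.6 | 11.0 | one |
| 92 | one-sided 0.05 | 5.5 | 6.9 | 8.3 | 9.6 | two |
| 102 | two-sided 95% | 6.2 | 7.5 | 8.7 | 10.0 | two |
| 102 | one-sided 0.05 | 5.0 | 6.3 | 7.5 | 8.7 | three |

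Wald limits are narrower. At n = 92, 4 v 6 gives 7.7 at one-sided 0.05 (passes) and 8.7 at two-sided 95% (fails). The range of one to three stands.

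**4. Illustration of differential detection (assumed inputs).** Suppose 92 evaluable per arm and true recurrence 12% v 4%, exactly at the margin. All control recurrences are detected, but only a fraction s of those in the non-fixation arm. The chance of declaring non-inferiority is Φ[(0.08 − (0.12s − 0.04))/SE − z_α].

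For s = 0.8, SE = √[(0.096 × 0.904 + 0.04 × 0.96)/92] = 0.0369, and Φ(0.024/0.0369 − 1.645) = 0.16.

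| s | One-sided 0.05 | One-sided 0.025 |
|---|---|---|
| 1.0 | 5.0% | 2.5% |
| 0.9 | 9% | 5% |
| 0.8 | 16% | 10% |
| 0.7 | 27% | 17% |

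The documents give no figure for s. The table shows sensitivity, not an estimate of actual bias.

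**The case against.** The protocol asserts the caller's blinding repeatedly. It does not say who packs the envelopes, who keeps the list, or whether the Study Secretary ever consults it, and a full protocol may name a separate holder. The patients who answer the calls are themselves blinded, and an early physical examination is made by a blinded surgeon. The text does not say that the caller alone decides who is called in. All of this stands. It limits the claim to a conflict between stated roles and stated blinding, but it does not remove that conflict: the protocol itself assigns the Study Secretary the randomization and a seat on the committee that reviews the videos. The Steering Committee's meeting frequency differs between sections (monthly in {9}, quarterly in {5d}), but the video review in {20c} is monthly and either frequency would expose the arm.

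Stronger readings that a reader might infer are not supported:

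- **The assessor is in fact unblinded.** The documents show incompatible assignments, not actual knowledge of the arm.
- **Interim results reveal allocation.** Sections {19} and {21b} mention access only, not results by arm or by code.
- **Enrolment reveals allocation.** "Enrolment will be performed by Study Secretary" concentrates roles, but allocation is learned when the envelope is opened in theatre.
- **The outpatient visit for suspected recurrence is unblinded.** The article does not say who examines. That is detail which a condensed article may leave out.
- **One missed recurrence decides the trial.** This holds in only one of the four Newcombe settings above.

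**Conclusion.** The concern holds as an internal contradiction and should be resolved. The role that ascertains the primary endpoint at 3 and 12 months is declared blinded. The same protocol has it run the randomization that ties codes to techniques, and seats it on the committee that watches code-labelled videos of mesh placement. No safeguard is described, so following the plan as written would defeat the blinding. Placing unblinding at the 12-month contact, without saying that the outcome is recorded first, adds to the problem.

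The size is conditional. With about 4 recurrences per arm, one to three further non-fixation recurrences separate a finding of non-inferiority from none. This rests on the assumed 4% rate, an absolute 8-point margin, 92 to 102 evaluable per arm, and a level and interval method that the article does not state. Whether ascertainment would actually differ between arms, and by how much, cannot be known from the documents.

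**What to change.** 1. Have an existing team member with no outcome role generate and hold the list and prepare the envelopes.
2. Have the remaining 3- and 12-month calls made by an existing team member who has not seen the list, the videos or arm-level data. Handing the list over is not enough for patients already randomised, because it does not undo what the present caller may have learned.
3. Exclude the caller from video review and from any interim data shown by arm.
4. State in {16a} and {17b} that the 12-month outcome is recorded before the patient is unblinded.
5. Describe the trial as participant- and assessor-blinded. The abstract's patient/surgeon label does not fit {17a}, where the surgeon is blinded only until the preperitoneal space has been created.

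**Cost:** a short amendment through the approvals in {25} and a reassignment of tasks among existing staff. Record the date of the change, so that calls made before and after it can be told apart.

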### Concealment mechanism {16b}

During the surgery, when the defect size is measured, the patient will be fully included in the study if M3 hernia is present. After the dissection of preperitoneal space (and establishing crucial checkpoints), surgeon will open a sealed, random envelope and find out what technique he/she will have to perform.

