### Intervention description {11a}

As M3 hernias are difficult to diagnose before the surgery, all patients scheduled for laparoendoscopic repairs will be asked to participate. After the dissection, reduction of hernia sack, and creation of preperitoneal space, the surgeon will open a sealed envelope and find out what technique he/she will have to perform and participants will be randomly allocated to one arm of the study. Dissection of preperitoneal space and placing the mesh in the groin area are considered to be the most important stage of the procedure—every surgeon will have to take visual record of that part of surgery to make sure proper technique was applied. Patients will not be aware of the method used during surgery. When using fixation material with histoacryl glue, it will be placed in previously predefined places (Fig. 2). Before recruiting patients, a 2-day “bootcamp” meeting was scheduled. Each center designated one surgeon responsible for conducting the trial in their hospital and sent him/her to attend the meeting. The meeting consisted of lectures on the first day and exhibition surgeries performed by experts on the second day. A meeting took place to unify the surgery technique and make sure every center will follow the same protocol. After operation, surgeon will fill the study form and put it in a sealed envelope. All patients in both arms will be given standard recommendation to avoid intensive physical activity for 2 weeks post-op. Standard wound care will be explained to patients in both groups.

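### The concealment item lets the operator open any sealed envelope: nothing requires numbered order or ties the patient to an envelope before it is opened

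*Protocol article*

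**What the plan says.** All references are to the protocol article.

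- **Sequence generation {16a}.** The Study Secretary produces a 1:1 list with a computer tool. From it, "204 envelopes will be prepared, each with a unique code number". Besides blank research cards, "there will also be a smaller envelope with the type of technique to be used during the procedure".
- **Implementation {16c}.** Each envelope's number comes from a computer program and is linked to one technique. "Surgeon will not be aware of the technique he should perform before opening the envelope". The same item says "Enrolment will be performed by Study Secretary".
- **Concealment mechanism {16b}.** Once an M3 hernia is confirmed and the preperitoneal space dissected, the "surgeon will open a sealed, random envelope and find out what technique he/she will have to perform".
- **Intervention description {11a}.** At the same step, "the surgeon will open a sealed envelope and find out what technique he/she will have to perform".
- **Participant timeline {13}.** Here "random allocation to the study arms will take place by opening the envelope and learning the technique to be used in a given participant".

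The envelopes are described as sealed, nested, uniquely coded and linked to a technique. They are not described as consecutive, as divided among centres, or as assigned to a patient before opening.

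**The concern.** A computer-generated list protects a trial in two ways: nobody can foresee the next assignment, and nobody can change it once it is due. Sealed, nested envelopes serve the first purpose. The second needs a rule that fixes which envelope belongs to the next patient. The concealment item states no such rule, and its only word on the choice of envelope is that it is random.

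The setting makes this more than a nicety. The envelope is opened in theatre, at 11 sites, by the operator, who by then has seen the size of the defect and how the dissection went. That operator works under a guideline which, according to Background and rationale {6a}, strongly recommends fixation for these defects. A surgeon uneasy about leaving a very large defect unfixed has a motive to look for a different assignment. Steering the hardest cases to glue would raise recurrence in the control arm and so favour non-inferiority.

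**Working it through.** **1. The plan's own figures.** The envelope count agrees with the target: 2 × 102 = 204. The sample size in Sample size {14} uses 4% recurrence (taken as equal in both arms), margin 8%, power 80%, significance 0.05 (sidedness not stated) and 10% loss:

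n per arm = (z₁₋α + z₀.₈₀)² × 2 × 0.04 × 0.96 / 0.08²

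- One-sided 0.05: n = 75. With 10% loss this is 75 × 1.1 → 83, or 75 / 0.9 → 84. The stated lower figure of 83 is reproduced.
- One-sided 0.025: n = 95. With loss this is 105 or 106, against the stated 102, so the upper figure is matched only to within about 3% (105).

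The order in which envelopes are used does not enter this formula. The sample size neither supports nor weakens the point.

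**2. Does a free draw bias allocation?** Suppose the operator draws blindly from 102 + 102 sealed envelopes and 184 are used (2 × 102 × 0.9 = 183.6). The expected share per arm is 0.50, and

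SD = √[184 × 0.5 × 0.5 × (204 − 184) / (204 − 1)] = √(46 × 20 / 203) ≈ 2.1 envelopes.

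So there is no bias and little overall imbalance. Harm needs something further: foreknowledge of an envelope's content, or an envelope opened and then not used.

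**3. What the wording permits.** Of the descriptions of this step, {16b} calls the envelope random, {11a} says only that it is sealed, and {13} refers to it without saying how it is chosen. {16a} and {16c} fix what each code contains but not when that code is used. Taking any envelope therefore complies, and use out of order is not a deviation that a monitor could flag. An envelope opened and set aside leaves a code with no patient, which shows only if someone compares all codes with the list. That comparison is not described. Criteria for discontinuing {11b} also allows excluded patients to be replaced while 204 envelopes exist for 204 participants, and it does not say what happens to the envelope of a replaced patient. A simple count at the end would therefore be hard to interpret.

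**4. How sensitive the result is.** With 102 × 0.9 ≈ 92 evaluable per arm, 4% gives 3.7, or about 4, recurrences per arm. The article does not name an interval method, so Newcombe's upper limit for the difference is an assumption here: d + √[(u_E − p_E)² + (p_C − l_C)²], with Wilson limits, z = 1.645 and margin 8%.

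| Events, experimental v control | Newcombe upper limit | Against 8% |
|---|---|---|
| 5 v 4 | 1.1% + 5.8% = 6.9% | pass |
| 6 v 4 | 2.2% + 6.1% = 8.3% | fail |

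With a Wald limit, 6 v 4 gives 7.7% and passes. With z = 1.96, Newcombe gives 6.8% for 4 v 4 (pass) and 8.3% for 5 v 4 (fail). One event can decide the outcome, but where the boundary lies depends on the method.

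These are events, not patients. If a difficult case has an assumed recurrence risk of 10% to 20%, redirecting one or two patients moves 0.1 to 0.4 expected events. Moving one whole expected event takes about 1/0.20 = 5 to 1/0.10 = 10 redirected patients.

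**5. Balance within centres.** Assume one unstratified 102/102 list spread over six centres of 19 and five of 18 (6 × 19 + 5 × 18 = 204). In 20,000 random permutations, a mean of 1.96 centres had at least two thirds of their patients in one arm, and 87% of permutations had at least one such centre. The result is the same if the envelopes are opened in strict order, so it bears on blocking by centre and not on selection.

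**The case against.** The strongest reply is that one loose word carries the point. In {16b}, a random envelope may simply mean a randomisation envelope, and {11a} and {13} do not use the word. No section says that the surgeon chooses from a stock or passes over the next number. This stands as far as intent goes: free choice is a permitted reading, not a stated procedure. But {16b} is the item that defines concealment, 11 sites have to follow it, and no other section supplies the missing rule. The enrolment role given to the Study Secretary in {16c} does not close the gap, since no contact with the Secretary is described when the envelope is opened.

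A reader might infer that the computer list does not determine who gets which technique. The documents do not support that. The list fixes the technique behind each code, and a blind draw from sealed, nested envelopes is still random allocation. Only the link between list order and patient order is missing.

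A reader might also infer that selection could never be found. That too goes too far. The codes are unique and tied to a technique, the operating record goes into a coded envelope ({13}), and surgical videos are filed by participant code and reviewed by the Trial Steering Committee ({20c}). Reconciliation is possible; it is just not described.

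Finally, an article often leaves logs and site instructions to the full protocol. The absence of a theatre log would not be a finding by itself. The point rests on what {16b} does state about the choice of envelope.

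**Conclusion.** The point holds as a weakness in the stated allocation procedure that should be corrected. It is not evidence that allocation is biased. Under {16b} any sealed envelope may be taken, at a moment when the operator knows how difficult the case is, and nothing binds the patient to a number beforehand. Departures from list order would therefore go unnoticed unless all codes were reconciled.

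Its size cannot be put as a figure, because bias requires conduct that the document neither describes nor implies. The few expected events (about 4 per arm, assuming 4% recurrence and 10% loss) explain why the safeguard matters. It would be tempting to say that redirecting one or two high-risk patients changes the conclusion. The arithmetic does not support that: the boundary moves with events, 5 to 10 redirected patients make one expected event at an assumed 10% to 20% risk, and the cut-off depends on an interval method and sidedness that the article does not state.

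The within-centre imbalance figures support blocking by centre only, and only if the list is unstratified and the centres recruit about equally. The article states neither. Such chance imbalance does not bias the overall comparison.

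**What to change.** Amend Sequence generation {16a}, Concealment mechanism {16b} and Implementation {16c} as follows:

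1. For the remaining envelopes, prepare a separate sequentially numbered series for each centre, with permuted blocks of varying size that are not disclosed to the sites.
2. Replace the random-envelope wording with a requirement to take the lowest unused number at that centre.
3. Have the patient code and the time written on the sealed inner envelope before it is opened.
4. Count every opened envelope as a randomised patient, including one whose patient is later excluded or replaced.
5. At the end, reconcile all 204 codes against the list, including those already used, and report the result.

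The cost is renumbering the remaining envelopes, a short site instruction, and a small recording duty in theatre. No extra patients are needed. Envelopes already opened cannot be put in order afterwards, so for them the reconciliation is the only safeguard.
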